## Methods and design

### Study design

The study has a prospective longitudinal matched cluster randomized single-blind multicenter design. Assignment to either the intervention group or the control group will take place through matched cluster randomization, on a care unit level (i.e. not on an individual level). Participants in the study will be followed for 24 weeks and will be assessed at regular intervals, viz., at baseline, six weeks, twelve weeks, and 24 weeks after baseline. A care organization enrolls two care units, in order to provide matching groups within a single care setting. One group will be a control group and receive care as usual; the other group will be an intervention group. Participants are blind to the intervention. Since receiving training and altering the daily nursing care is part of the intervention, care-givers such as the nursing staff cannot be blind for the intervention. The examiners will be blinded.

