### Sample size

To calculate the number of participants needed, a power analysis is performed. The primary outcome variable (QoL) is used to calculate the power and a linear time effect is assumed for both intervention and control conditions. A difference on total score of 10 points after 24 weeks is considered clinically relevant. This equals to a difference of 2.5 points per 6 weeks. After running simulations with a known total variance of 300 and a mean score of 80 (pilot data), a sample size of 200 participants (spread over 10 care organizations and 10 participants per care unit) is needed. Allowing for 10% dropout, this means (200 × 10/9 =) 224 participants need to be included in the study.

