### Covariates

Participants’ characteristics that might be of influence are taken into account. These covariates are age, gender, educational level, and ApoE4 status.

The highest educational level is classified by the Verhage scale [31]; a seven point rating scale. A score of 1 equals a level of less than six years of elementary school; score 2 stands for completed elementary school; a score of 3 indicates more than six years of elementary schools and less than three years of secondary education; score 4 is indicative of elementary school and three years secondary education; score 5 stands for elementary school and four years of secondary education; score 6 represents pre-university education and/or higher vocational education; and a score of 7 stands for a finished training at a university or technical college.

Genetic susceptibility for dementia as indicated by ApoE4 genotype, is assessed by collecting buccal cells. Two Catch-all TM collection swabs (Epicentre, Madison, Wisconsin, USA) per participant are used.

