### Statistical analysis

The data from this prospective longitudinal matched cluster randomized single-blind multicenter study will be analysed using a linear mixed model. The fixed effects are *‘condition’* and *‘time’*; the linear ‘*condition x time’* interaction is the effect parameter of interest and *‘care unit’* and *‘participant (within the care unit)’* are the random effects (both intercepts and slopes). An intention to treat analysis will be performed.

The baseline (cross-sectional) data will also be analysed for Pearson’s and/or Spearman’s coefficients, to establish correlations between the primary outcome variable QoL and the secondary outcome variables (viz., cognition, mood, independence, rest-activity rhythm, blood pressure, and masticatory function). Additionally, linear regression analyses will be performed to study the independent contribution of the various secondary outcome variables to QoL.

A baseline comparison will be performed to make sure that the intervention group and control group are similar with regards to variables that are not of primary interest (i.e. the covariates and confounders) and the outcome variables. Any difference between the groups afterwards is then likely due to the intervention. If there are differences between the groups prior to the intervention, the baseline scores will be incorporated as covariates in the analysis.

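### Baseline scores enter the primary model only if the groups are seen to differ; entered as a plain covariate, they would not remove the effect of a chance imbalance on condition x time

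*Protocol article*

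**What the plan says.** All of this is in the Protocol article. Under Statistical analysis the model is a linear mixed model with condition and time as fixed effects and random intercepts and slopes for care unit and participant. The linear condition x time "interaction is the effect parameter of interest". Under Study design, assessments take place "at baseline, six weeks, twelve weeks, and 24 weeks after baseline", so the baseline score is one of the four repeated measurements.

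The same section then says: "A baseline comparison will be performed to make sure that the intervention group and control group are similar" on the covariates, the confounders and the outcome variables. From that similarity it concludes: "Any difference between the groups afterwards is then likely due to the intervention". If similarity fails, the rule is: "If there are differences between the groups prior to the intervention, the baseline scores will be incorporated as covariates in the analysis". It does not say what counts as a difference, which scores then enter, or in what form.

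The Covariates section separately names characteristics to be taken into account: "These covariates are age, gender, educational level, and ApoE4 status". The model description does not mention them.

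**The concern.** There are two problems.

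First, the model for the primary outcome is chosen after looking at the data. With randomised care units, a later difference can be attributed to the intervention because of the randomisation, not because a baseline table looked even. A comparison that finds no difference is weak evidence of similarity, and one that finds a difference may reflect chance alone.

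Second, the remedy does not match the effect parameter. The condition main effect already absorbs a difference in level at week 0. What remains is regression to the mean: part of a chance difference at week 0 is measurement noise that is absent at later visits, and the fitted slopes pick this up. A covariate that is constant over time shifts levels and leaves slopes alone. The team could believe that an imbalance had been handled when the estimate still carried it.

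**Working it through.** **Inputs from the Protocol article.** Two care units in each of 10 organisations with 10 participants per unit: 10 x 2 x 10 = 200, or 10 units and 100 participants per arm. Visits at weeks 0, 6, 12 and 24, that is t = 0, 1, 2, 4 in 6-week units. Total variance 300. Target: "A difference on total score of 10 points after 24 weeks is considered clinically relevant", which is 10/4 = 2.5 per 6 weeks. Dropout 10%; 200 x 10/9 = 222.2, stated as 224. The 200 itself cannot be re-derived, because Sample size gives no error level, power, intraclass correlation or variance split. Only the numbers of units and participants are used below.

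**Assumptions (middle case, not in the document).** The variance of 300 is split into care-unit intercept 15, participant intercept 135 and residual 150. Slope variances are 1 (unit) and 4 (participant). Intercepts and slopes are independent. Tests are two-sided at 5%.

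**Step 1: does a baseline main effect change condition x time?** With equal clusters and complete data, each participant reduces to an intercept and a slope. The baseline term enters only the intercept equation. The regressors of the slope equation are then a subset of those of the intercept equation, so its generalised least squares estimate is the plain difference in mean slopes, with or without the term. This result does not depend on the variances.

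A simulation check used 300 null trials per scenario, with unit variance 15, within-person correlation 0.6, slope SDs 1.0 and 0.5, and intercept-slope correlation -0.3. Changes are in points per 6 weeks:

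- Balanced, complete: largest change 3e-14.
- Unequal clusters, complete: largest change 0.005.
- 10% dropout: mean absolute change 0.036 (0.036/2.5 = 1.4% of target), largest 0.13 (5%), or 0.21 (8%) with unequal clusters as well.

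The dependence of the estimate on baseline imbalance was -0.075 per point both without and with the term (complete data), and -0.077 against -0.076 (10% dropout). Adding baseline x time as well brought it to about +0.02.

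**Step 2: size of the dependence (middle case, complete data).**

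- Mean of t = 1.75; sum of squares = 3.0625 + 0.5625 + 0.0625 + 5.0625 = 8.75. Weight of week 0 in the slope = -1.75/8.75 = -0.2.
- Covariance of slope contrast and baseline imbalance = 2 x (-0.2) x 150/100 = -0.6.
- Variance of the imbalance = 2 x (15/10 + 285/100) = 8.7; SD = 2.95.
- Dependence = -0.6/8.7 = -0.069 per point per 6 weeks.
- For a 5-point imbalance (5/2.95 = 1.7 SD): -0.069 x 4 x 5 = -1.4 points at 24 weeks, 14% of the target.

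With the unit variance kept at 15 and the total at 300, residual 90 gives -0.36/8.7 = -0.04 and residual 210 gives -0.84/8.7 = -0.10.

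**Step 3: precision with a common week-0 mean.**

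- Free baseline: 2 x (1/10 + 4/100) + 2 x 150/(100 x 8.75) = 0.280 + 0.343 = 0.623.
- Variance of the condition contrast at week 0: 2 x (15/10 + 135/100) + 3 x (1/4 + 1.75²/8.75) = 5.7 + 1.8 = 7.5. Its covariance with the slope contrast is -0.6.
- Common baseline: 0.623 - 0.6²/7.5 = 0.623 - 0.048 = 0.575, about 8% lower. The dependence on imbalance is zero.
- Power, from 2.5/sqrt(variance) - 1.96: 89% against 91%.

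**Step 4: the three-visit alternative.** Take weeks 6, 12 and 24 as outcomes, with baseline and baseline x time as covariates, and keep a condition main effect. The sum of squares of t = 1, 2, 4 is 16/9 + 1/9 + 25/9 = 4.667. The variance is 0.280 + 3/4.667 = 0.923, and power falls to about 74%.

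**Step 5: how often the rule would fire.** If a difference meant p < 0.05 and the tests were independent (both assumptions), the chance of at least one is 1 - 0.95^k: 5% for k = 1, 26% for 6, 46% for 12, 64% for 20, 75% for 27.

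**The case against.** The strongest reply is that the underlying model is sound. Condition x time, fitted without any baseline term, is unbiased over randomisations, so the -1.4 points is a shift conditional on an imbalance seen in about 9% of trials (two-sided). If the triggered term hardly moves the estimate, the trigger can do little harm to it. The article also does not say how baseline scores would enter, and detail of that kind can sit in a fuller plan.

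Much of this stands. It limits the harm and rules out several stronger readings that a reader might infer:

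- **That a baseline covariate cannot change the estimate.** This is exact only for a main effect with complete balanced data. The plan expects 10% dropout, where the estimate moves a little, though not so as to correct the imbalance. With baseline x time the statement fails.
- **That the rule would almost certainly fire.** About 40 independent tests at 5% would give 87%, but the article names no test, threshold or count, and the outcomes are likely to be correlated.
- **That Covariates and Statistical analysis contradict each other.** The conditional sentence concerns baseline scores. It does not say that age, gender, education and ApoE4 enter only after a difference is seen. The wording is unclear, no more.
- **That any baseline difference must be chance.** Units are randomised, but participants consent individually, unblinded nursing staff deliver the care, QoL is rated by a proxy, and the order of allocation, consent and baseline is not stated.

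The reply does not rescue the rule. The article itself makes the model conditional on observed data, and in its natural form the remedy does not do what it is there for.

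**Conclusion.** The concern holds in a limited form and should be fixed. The primary model is not fixed in advance. Read as a main effect, the conditional adjustment leaves condition x time unchanged with complete balanced data and moves it by about 1.4% of the target on average with 10% dropout. Its dependence on a chance imbalance stays the same. In the middle case that dependence is worth about -1.4 points at 24 weeks for a 5-point imbalance, and a common baseline mean would lower the variance by about 8%.

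The invariance with balanced complete data is exact. The other sizes rest on assumed variance components. They are also on the scale of the Sample size section, whose pilot mean of 80 lies above the 57-point maximum in Outcome variables, so they are best read relative to the 10-point target. A reader might infer that the primary result would be biased; the documents do not support that. The cost is conditional error, some lost precision and a choice of model left open until the data are seen.

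**What to change.** - Delete the conditional sentence. Always fit the longitudinal model with one common week-0 mean for both conditions, so that condition enters only through condition x time, whatever the baseline comparison shows.
- If weeks 6, 12 and 24 are instead used as outcomes with baseline and baseline x time as covariates, drop the condition main effect; otherwise precision falls (Step 4).
- State whether age, gender, education and ApoE4 are always in the primary model.
- Keep the baseline table descriptive, and remove the inference that observed similarity is what makes later differences attributable to the intervention.
- Keep the free-baseline model as a sensitivity analysis.

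The cost is wording only, with no new data. There is one small downside: a common week-0 mean assumes that baseline was measured before the intervention could affect it and that recruitment within units did not depend on allocation. The article does not give that order of events, so it should be stated alongside the model.

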### Ethical considerations

This study is approved by the Medical Ethical Committee of the VU University Medical Centre (METc VUmc; ref: **2010–342**) according to the Declaration of Helsinki (2008). The research has been included in the general assessment and registration form (ABR form) (ref: NL33230.029.10) and in the Netherlands National Trial Register (NTR) (ref: NTR1561).

## Discussion

The described study is a prospective longitudinal matched cluster randomized single-blind multicenter study, investigating the effect of an intervention aimed at increasing masticatory activity by increasing and improving oral health care and the consistency of the diet. Participants in this study are elderly people suffering from dementia and receiving institutionalized care. The intervention is performed by daily nursing staff.

Strengths of this design are the direct clinical applicability of results; a transfer to the clinic does not need to be made since all work is done in a clinical setting. The intervention is performed by the nursing staff, allowing immediate assimilation into daily care. By taking baseline measurements and also repeated follow-up assessments, a thorough insight into the effect of the intervention is obtained. Chance findings are less likely to occur, and the effect over time can be made clear. The broad spectrum of data collection allows for a further widening of the research scope. Besides QoL, important variables such as cognition, mood, independence, and the rest-activity rhythm are assessed. Also, the research methods are varied; both qualitative and quantitative measures are used. By combining these two research methods, we obtain both quantitative, objective data about ‘how’ the intervention is effecting the outcome variables and qualitative, more subjective data, which is descriptive and can provide insight into the ‘why’ an intervention does or does not have an effect. Quantitative data can provide insight in effect sizes and underlying mechanisms, is not subject to interpretation and not dependent on a proxy’s mood and cognition (e.g., [13]). Nonparametric testing, used for qualitative data, is stricter and therefore if results are found, they tend to be more robust. The heterogeneity of the research population is (partly) eliminated by matching and cluster randomizing the care units.

There are of course also some aspects of the study design that might prove to be shortcomings. The Consolidated Standards of Reporting Trials (CONSORT) guidelines [56] include the practice of blinding of participants, the nursing staff, and the assessors. However, since the nursing staff in this protocol plays a vital role in providing the altered care as the intervention agents, they cannot be blinded. A placebo treatment which resembles oral health care in such a way that the nursing staff would not notice the difference without actually being effective is, to our knowledge, not available. The same holds true for the participants; there is no placebo treatment available and therefore, participants in the control group receive ´care as usual´. This ´care as usual´ for dependent elderly could, and one might even argue, should, include oral health care, but it has been shown that this is often unfortunately not the case (e.g., [26,28,57-60]). In contrast to the nursing staff and the participants, the trained examiners are blinded for the participants’ allocation in either the intervention or control group.

There will also be a certain amount of variety in the nature of interventions due to local differences in nursing homes. For example, the presence of a dentist or dental hygienist and/or the possibility to cook rather than order meals, will shape the specific details of the local intervention. This flexibility might be perceived as a weakness in the study design, because the intervention is not uniform across the several care facilities; however, a practical implementation of any findings would be subject to the same factors, making the study design clinically relevant. Furthermore, the use of matched cluster randomization, with one care organization always providing both an intervention and control group, is a good way to control for this variation. In the CONSORT guidelines, this design is described as stratification by center and is considered appropriate to control for differences such as can occur in multicenter studies [56].

Effects in the increased food consistency group cannot be attributed to mastication per se, but can also be considered as an effect of the changed diet, enhancing for example, vitamin intake. Similarly, any effects of oral health care cannot purely be attributed to increased mastication; for example lowered incidence of oral pain or inflammation might also have effects on QoL. Despite these limitations, we argue that the outcomes of this study will point the direction for further research into these areas and will provide important insights in the topic of gerodontology in particular and dementia care in general.

## Abbreviations

AD: Alzheimer’s disease; ADL: Activities of daily living; ApoE: Apolipoprotein E; CMAI: Cohen-mansfield agitation inventory; CONSORT: Consolidated standards of reporting trials; CSDD-D: Cornell scale for depression in dementia; DLB: Dementia with Lewy bodies; FTD: Frontotemporal dementia; IS: Interdaily stability; IV: Intradaily variability; L5: 5 Least active hours; M10 10: Most active hours; mmHg: Millimeters of mercury; MMSE: Mini mental state examination; MVBF: Maximal voluntary bite force; QoL: Quality of life; RA: Relative amplitude; RAI: Resident assessment instrument; SES: Socioeconomic status; VaD: Vascular dementia; VU-BFG: VU University bite force gauge.
